## Results

This project was successfully funded by the Health Care and Promotion Fund (Project No. 08150345) of the Food and Health Bureau, Hong Kong government, in March, 2016 after a stringent external review process. Enrolment of participants will start in October, 2016 and results are expected by June, 2018.

It is anticipated that the technology-based injury prevention intervention will yield a small to medium effect in terms of mothers’ child safety knowledge enhancement. It is estimated that intervention participants will spend more time on the mobile app than on the website. Dose-response relationships between the outcome measures and the website and mobile app usage will be examined. It is expected that intervention participants will have better age-appropriate safety knowledge, attitudes, intentions, perceived behavioral control, and actual behavior related to home safety practice compared to the control group participants.

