**Methods:**

In this randomized controlled trial, 308 mothers will be recruited from the antenatal clinics and postnatal wards of two major public hospitals in Hong Kong. Participating mothers will be randomly assigned into intervention and control groups. Mothers in the intervention group will be given free access to a technology-based injury prevention program with anticipatory guidance, whereas mothers in the control group will be given a relevant booklet on parenting. The injury prevention program, available as a website or on a mobile app, includes behavioral components based on the Theory of Planned Behavior. The primary outcome measure will be the change in the mother’s knowledge of child safety. The secondary outcome measures will be age-appropriate domestic safety knowledge, attitudes, intentions, perceived behavioral control, and self-reported behavior related to home safety practice. We will also determine dose-response relationships between the outcome measures and the website and mobile app usage.

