**Results:**

Enrolment of participants will begin in October 2016. Results are expected by June 2018.

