## Methods

### Study Design

This study will be a randomized controlled trial of the effectiveness of a technology-based injury prevention program for enhancing mothers’ knowledge of child safety (Figure 1). Mothers will be recruited from the antenatal clinics and postnatal wards of two major public hospitals in Hong Kong: Kwong Wah Hospital and Queen Mary Hospital. Between October, 2016 and January, 2017, nurses will identify potential participants. An experienced research assistant will provide the participants with an information sheet explaining the study, along with a consent form. The inclusion criteria will include mothers attending the antenatal clinics or staying in the postnatal wards at Kwong Wah Hospital or Queen Mary Hospital. The exclusion criteria will include subjects unable to read Chinese, and those without Internet access.

Participants will be randomly allocated into the intervention and control groups in a 1:1 ratio. All participants will be given an information pack consisting of a parenting booklet from the Maternal and Child Health Centers (MCHC). This booklet is publicly available and provides brief and general home safety tips for mothers with children under 3 years of age. The intervention group will also be given an additional leaflet containing a brief introduction to the Internet-based domestic safety platform, and instructions on how to access the website. Mothers can easily access this practical online parenting resource through the website or a mobile app. The online resource contains information on various safety topics and educational materials, including general and age-appropriate injury prevention measures suitable for mothers with infants and children between 2 and 18 months of age. Participants in the intervention group will be periodically contacted by telephone and electronic messaging to encourage them to access and engage with the domestic safety website. The research team will provide technical support to all participants who encounter problems accessing the intervention website or mobile app. Apart from technical support, no other intervention will be provided to those accessing the website or mobile app by any therapist, nurse, care provider, or physician. The control group will receive only the MCHC parenting booklet.

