All consenting participants will be asked to complete a general safety questionnaire at the antenatal clinic or postnatal ward of the two hospitals. Age-appropriate safety knowledge, attitudes, intentions, perceived behavioral control, and self-reported behavior related to home safety practice will be assessed at specific child developmental ages at 2, 6, 9, 12, and 18 months. Participants in the intervention group will be given immediate feedback on their specific injury prevention behaviors prompted by the *at-risk* (incorrect) answers obtained from their completed questionnaire. This online feedback counseling approach aims to educate mothers and enhance their awareness related to domestic injury prevention. At the end of the counseling session, each intervention participant will be provided with age-appropriate safety information. Participants’ general safety knowledge will be reassessed when their children reach the age of 18 months. Intervention participants will be reminded by telephone and email to complete the age-appropriate safety questionnaires at each developmental stage, and the final general safety questionnaire. Control group participants will be contacted using the same schedule, to remind them to read the booklet and to complete the questionnaires.

This study is registered with Clinicaltrials.gov (Identifier: NCT02835768) and has been approved by the Institutional Review Board of Hong Kong University and Hospital Authority Hong Kong West Cluster (Reference number: UW 15-465). All participants will provide written informed consent.

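### The recruitment window, the 18-month primary reassessment and the June 2018 results date cannot all hold

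*Protocol article*

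**What the plan says.** Four statements in the protocol article bear on the timeline.

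- **Recruitment window (Methods, Study Design):** "Between October, 2016 and January, 2017, nurses will identify potential participants".
- **Who is recruited (same section):** "The inclusion criteria will include mothers attending the antenatal clinics or staying in the postnatal wards". Some children are therefore newborn at enrolment and others not yet born. No gestational age limit and no antenatal share are given.
- **Timing of the endpoint (same section):** participants' "general safety knowledge will be reassessed when their children reach the age of 18 months". The Abstract names change in the mother's child safety knowledge as the primary outcome, and Measures assigns the evaluation of change in general knowledge to this questionnaire. The age-appropriate outcomes "will be assessed at specific child developmental ages at 2, 6, 9, 12, and 18 months", so the last of these falls at the same age.
- **Reporting date:** the Abstract says "Enrolment of participants will begin in October 2016. Results are expected by June 2018", and the Results section gives the same two dates: "Enrolment of participants will start in October, 2016 and results are expected by June, 2018".

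Sample Size Calculation asks for 92 evaluable mothers per arm (d=0.42, 80% power, 5% significance level). It recruits 154 per arm to allow for 40% attrition.

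**The concern.** The endpoint is tied to the child's age, so the earliest date on which the full primary data set can exist is the last child's birth date plus 18 months. The last stated month of recruitment puts that date after June 2018, before any allowance for reminders, data cleaning or analysis. Recruiting women who are still pregnant moves it later again.

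If June 2018 were treated as binding, mothers recruited late, and those recruited well before term, would have no primary outcome for purely administrative reasons. The attrition allowance does not cover this. It was set for loss between the two evaluations, whereas this shortfall concerns mothers who are still in follow-up but not yet due.

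**Working it through.** **Inputs.** From the documents: recruitment October 2016 to January 2017, reassessment at 18 months, results by June 2018, 308 mothers, 40% attrition, d=0.42. Assumed: the window runs from 1 October 2016 to 31 January 2017 (123 days) with uniform enrolment; postnatal mothers are enrolled on the day of birth; the deadline is read generously as 30 June 2018; attrition is unrelated to birth date; power is for an unadjusted two-sided two-sample t-test at 5%.

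**Step 1. The plan's own sample size.** For d=0.42 and 80% power the normal approximation gives 89 per arm and the t-test gives 90, close to the stated 92. Inflation: 92 / (1 − 0.40) = 153.3, so 154 per arm and 308 in total. The sample size reproduces and is not in question here.

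**Step 2. Latest assessment date.** Date = enrolment date + weeks of pregnancy left + 18 months. For a mother enrolled on 31 January 2017:

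| Weeks of pregnancy left | Birth | Child aged 18 months |
|---|---|---|
| 0 (postnatal ward) | 31 Jan 2017 | 31 Jul 2018 |
| 4 | 28 Feb 2017 | 28 Aug 2018 |
| 12 | 25 Apr 2017 | 25 Oct 2018 |
| 20 | 20 Jun 2017 | 20 Dec 2018 |
| 28 | 15 Aug 2017 | 15 Feb 2019 |

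The first row needs no assumption about gestation and already falls after June 2018.

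**Step 3. Share reaching 18 months by 30 June 2018, all mothers postnatal.** Children must be born by the end of December 2016. Enrolment days from 1 October to 31 December number 92, and 92 / 123 = 74.8%. The remaining 31 / 123 = 25.2%, about 78 of 308, would not be due. With a deadline of 1 June instead, about 50% would not be due.

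**Step 4. Precision if the analysis closed on 30 June 2018.** Evaluable per arm = 308 × share × 0.6 / 2. All postnatal: 308 × 0.748 × 0.6 / 2 = 69. Power at 69 per arm with d=0.42 is about 69%.

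**Step 5. Range with antenatal recruits.** Illustration only: half the sample is antenatal (assumed), with weeks of pregnancy left spread uniformly over the range shown (assumed). The mixed share is the average of 74.8% and the antenatal share.

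| Weeks left, antenatal half | Antenatal share reaching 18 months | Mixed share | Evaluable per arm | Power |
|---|---|---|---|---|
| 0–4 | 63% | 69% | 64 | about 65% |
| 0–12 | 41% | 58% | 54 | about 58% |
| 0–20 | 25% | 50% | 46 | about 51% |
| 0–28 | 18% | 46% | 43 | about 48% |

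The documents do not say which row applies, if any.

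**The case against.** The strongest reply is that June 2018 is a forecast. The Abstract says only "Results are expected by June 2018". Nowhere does the article set a data cut-off, an early close of follow-up or an interim analysis, and the 18-month reassessment carries no calendar limit. If that rule is followed, results simply arrive later, and the endpoint, sample size and analysis are untouched. This stands. It is why the power figures above are conditional and why the point is moderate. It does not remove the conflict between the stated dates, which nothing in the article reconciles.

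A reader might infer more than the documents support, in four ways:

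- **That most antenatal recruits would be lost.** Gestation at recruitment is not given. With 0–4 weeks left, 63% of them would be due by 30 June 2018.
- **That power would fall to about half.** The 48% and 51% figures need an assumed antenatal share, an assumed gestation and a June cut-off. In addition, Data Analysis plans covariate-adjusted regression for intervention effectiveness, whereas the power here is for an unadjusted t-test.
- **That the 18-month endpoint would be shortened without notice.** Nothing in the text suggests this.
- **That the comparison would be biased.** Allocation is 1:1 and randomized within hospital, so a cut by birth date should fall on both arms alike.

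Appealing to the attrition allowance or to the intent-to-treat approach does not answer the point. The first covers a different loss, and the second cannot supply a measurement that is not yet due.

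**Conclusion.** The inconsistency is real and rests on the article's own dates. The primary outcome cannot be complete before about 31 July 2018, and not before about December 2018 to February 2019 if women with 20 to 28 weeks of pregnancy left are enrolled at the end of the window.

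The consequence is conditional. Only if the analysis were closed at 30 June 2018 would at least about 25% lack the primary outcome, leaving at most about 69 evaluable per arm and about 69% power. These bounds assume uniform enrolment: recruitment concentrated early would lose fewer mothers, and recruitment concentrated late would lose more. Antenatal recruitment lowers the figures by an amount that the documents do not allow one to fix. The harm would be reduced precision and a sample shifted towards early and postnatal recruits, not a distorted contrast between arms. Severity: moderate.

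**What to change.** In the Abstract and in Results, replace June 2018 with a date that follows the last enrolled child's 18-month assessment. This is not before August 2018, and may be as late as about early 2019 if women far from term are enrolled. The gestation range accepted at the antenatal clinics settles where in that range it falls. Add one sentence saying that the primary analysis waits for that last assessment.

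The cost is a text change, a notice to the funder and results some months later. No further participants or visits are needed.

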## Discussion

This study examines the effectiveness of a technology-based intervention designed to improve mothers’ awareness of the severity and consequences of domestic injuries. Mothers can enhance their knowledge of child safety by accessing the online age-appropriate information related to child health, parenting, and safety. This technology-based platform can help users find available resources, services, providers, and relevant contact information.

A discussion forum will be available on the new website and mobile app as a means to facilitate communication between mothers and professionals. Mothers can also benefit from technology-mediated social support and chat rooms, and exchange lay knowledge. Safety experts and pediatricians will be invited to provide advice, professional support, and counseling through the website and the app, which will strengthen online services and promote engagement. The website will help to mobilize community stakeholders to address child safety concerns and other aspects of child health, and will allow stakeholders to raise their own concerns. The website will empower parents to take responsibility for their children’s health and safety, and to adopt good health practices.

The Internet is becoming widely accepted as an effective, low-cost platform for the dissemination of health and safety information. In comparison to traditional media, information on the Internet can be updated instantly and inexpensively [34]. Electronic dissemination of information has a great deal of potential when compared to traditional media, especially when considering the speed of information propagation, because it has the ability to reach a large audience and connect with those who might otherwise be difficult to approach [35]. Technology-based interventions can also serve as platforms for viral campaigns, which involve sharing knowledge among information seekers. This easily accessible online safety platform (intervention website and mobile app) containing comprehensive up-to-date information on childhood safety will educate parents and caregivers, and encourage them to adopt safer practices. Findings from the study will contribute to good health practices, future research, and the development of user-friendly online information platforms. For example, the educational effort of CIPRA could be enhanced by combining other approaches, including legislative measures and infrastructure improvements, because a solely educational approach is limited in reach. Our main goal is to provide an effective online educational platform to be funded on an ongoing basis, which will be incorporated into the Maternal and Child Health Services under the Department of Health, and into postnatal clinics in public hospitals.

This study will be carried out in collaboration with CIPRA by sharing resources, exchanging best practices, and combining efforts towards sustainability. Furthermore, this Web-based intervention will demonstrate a sustainable health promotion strategy that mobilizes local resources with cross-sectoral collaborations to engage the community by building partnerships between private, public, and nongovernmental organizations. Upon completion of the evaluation, the information leaflet with details of the domestic safety website will be disseminated to relevant public, private, and nongovernmental organizations that promote child health, and particularly child safety. This freely accessible safety platform will allow organizations to reinforce awareness and promote domestic injury prevention among target populations.

Information on the platform can be revised regularly to ensure that users have access to high quality, up-to-date, and accurate information. All safety information contained on the website and mobile app will be shared with interested nongovernmental organizations, MCHC, and postnatal clinics. All information associated with the platform can also be linked across sectors, including the government, academic institutions, nongovernmental organizations, and private sectors in Hong Kong. The CIPRA safety information website and mobile app are expected to be easily accessible for all users, including parents, caregivers, school teachers, social workers, children, and nonacademic medical and allied health professionals. This platform will serve as an information hub for the community and a learning platform for all relevant stakeholders. When disseminating the findings from the intervention study within the community, we will also compare the intervention with other services by collecting feedback from different users, interviewing relevant stakeholders, and conducting ecological and econometric studies to assess the long-term social impact on the intervention. We will further improve the intervention platform to meet the needs of the community.

Anticipatory guidance for injury prevention should be provided to parents along with routine medical care, such as well-child visits for infants and children. An important advantage of this Internet-based intervention, apart from providing anticipatory guidance, is its potential to reach a wide audience, which can be exploited by other electronic health services that utilize community-wide interventions with intersectoral collaborations between public, private, and nongovernment organizations. The use of technology-based interventions is increasing, and can be considered a powerful mobilization strategy for engaging various user groups. In the future, the online platform can be adapted to deliver preventive pediatric health care information in other learning areas, such as growth monitoring, nutrition, and vaccinations. All of these important child health-related areas would contribute to the establishment of a child health portal that will help to promote the well-being and optimal development of children in Hong Kong.

## Appendix

Multimedia Appendix 1 General safety knowledge questionnaire.

Multimedia Appendix 2 Age-appropriate safety questionnaire.

Multimedia Appendix 3 Injury prevention behavior checklist.

Multimedia Appendix 4 Website and mobile app user acceptance questionnaire.

Multimedia Appendix 5 The peer-review report from the Health Care and Promotion Fund.

Multimedia Appendix 6 CONSORT-EHEALTH checklist (V1.6.1) [36].

## Abbreviations

CIPRA: The Hong Kong Childhood Injury Prevention and Research Association
MCHC: Maternal and Child Health Centers
TIPP: The Injury Prevention Program
